## Materials and methods

Study design and setting

This study will be conducted as a parallel-designed, prospective, assessor-blinded, single-center randomized controlled trial. The timeline of this protocol study is from August 2024 to May 2025. This study will take place at the Department of Tui Na and the Psychosomatic Medicine Outpatient Department of the First Teaching Hospital of Tianjin University of Traditional Chinese Medicine, China. Seventy GAD patients will be randomly allocated to either the combined abdominal massage and medication group or the medication-only group. The study will involve various scale assessments, EEG examinations, and stool sample collections both pre- and post-intervention. Additionally, 35 healthy participants will be recruited to serve as normal controls and will undergo relevant tests and examinations upon enrollment. The trial flowchart is depicted in Figure 1, and the study timeline is outlined in Figure 2.

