**Figure 3 FIG3:**
[figure not shown]
Acupoint location diagram.

Control Group GAD Patients

Medication includes oral escitalopram (Bailex) (Sichuan Kelun Pharmaceutical Co., Ltd., China; approval no.: National Drug Standard H20080788; specification: 10 mg × 10 tablets), 10 mg once daily at 09:00 AM for eight weeks.

Healthy Participants

Healthy participants will not receive any treatment. They will be screened based on their medical history and HAMA scores. General information and HAMA scores will be recorded. Upon enrollment, EEG and stool samples will be collected from healthy participants.

Statistical analysis

This study will conduct statistical analysis based on the principle of intention-to-treat (ITT), including all patients who entered randomization and were not excluded in the statistical analysis. The efficacy endpoints will be analyzed using the full analysis set (FAS), supplemented by the per-protocol set (PP). Safety endpoints will be analyzed using the safety set (SS).

IBM SPSS Statistics for Windows, Version 26 (Released 2019; IBM Corp., Armonk, New York, United States) will be used for statistical processing. Measurement data will first be tested for normal distribution and homogeneity of variance. Data that meet the normal distribution and homogeneity of variance will be statistically described using the mean ± standard deviation (x̄±s), and data that do not meet the normal distribution and homogeneity of variance will be statistically described using the median (M) and the 25th and 75th percentiles (P_25_, P_75_).

For the comparison of measurement data between two groups, a paired two-sample t-test will be used for data that meet the normal distribution, and a rank-sum test will be used for data that do not meet the normal distribution. For the comparison of data at different time points after treatment with pre-treatment data, a paired t-test will be used for data that meet the normal distribution, and a rank-sum test will be used for data that do not meet the normal distribution. For the comparison of measurement data among multiple groups, a one-way ANOVA will be used for data that meet the normal distribution, and a rank-sum test will be used for data that do not meet the normal distribution.

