For the comprehensive comparison of measurement data at different time points between two groups, a repeated measures ANOVA will be used if the data meet the sphericity assumption and a Friedman test will be used if the data do not meet the normal distribution. Count data will be statistically described using case number and composition ratio, and the comparison between groups will be performed using the χ² test. Rank data will be analyzed using the two-sample non-parametric rank-sum test. The significance level for all tests will be α=0.05.

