## Results

Primary outcome

The primary outcomes of this study will be determined by the HAMA [18] scores and electroencephalogram (EEG) results. The HAMA scale consists of 14 items, which will be evaluated by professional psychiatrists before and after the treatment. The total HAMA score can range from 0 to 56, with anxiety levels classified as follows: possible anxiety for scores between 7 and 14, definite anxiety for scores between 14 and 21, moderate anxiety for scores between 21 and 29, and severe anxiety for scores greater than 29.

For the EEG, participants will be seated in a quiet environment, with their eyes closed, while maintaining an alert state. Scalp electrodes will be placed according to the international 10-20 system, using 17 disc electrodes with earlobes serving as reference electrodes. The EEG will record both bipolar and reference leads, with standard evoked tests (including hyperventilation, rhythmic photic stimulation, and eye-opening/closing tests) conducted during monitoring. The time constant will be set at 0.3 ms, the high-frequency filter will be set at 70 Hz, the standard voltage will be set at 10 mV/mm, and the recording time will be between 15 and 20 minutes.

Other outcome measures

Other outcome measures in this study include symptom signs, scores on the Hamilton Depression Rating Scale (HAMD), scores on the Symptom Checklist-90 (SCL-90), and results from monitoring the gut microbiota.

Hamilton Depression Rating Scale

This scale is used to assess the severity of depression in patients and consists of 17 items. Depression severity is classified based on HAMD scores as follows: a score of less than 7 suggests no depression; a score between 7 and 16 suggests possible depression; a score of 17 or greater indicates definite depression.

Symptom Checklist-90

This scale is used to evaluate patients' self-perceived symptoms during treatment. Each question is rated on a scale from 1 (none) to 5 (severe), with higher scores indicating more severe adverse symptoms.

Gut Microbiota Monitoring

Stool samples will be collected from randomly selected patients in the treatment and control groups before and after eight weeks of treatment. Samples will be collected in the morning, on an empty stomach, using a sterile spoon to obtain 3-5 g of fresh stool. These samples will be immediately placed in standardized sterile containers and stored at -80°C for subsequent analysis [19].

Safety assessments

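### The non-normal fallback for comparing the two arms over time is the Friedman test, which has no between-group term and so tests change over time, not the treatment effect

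*Protocol article*

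**What the plan says.** All the relevant text is in the protocol article.

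- **The question.** The Statistical analysis section sets out one procedure for data collected over time in both arms: "For the comprehensive comparison of measurement data at different time points between two groups".
- **The parametric method.** "a repeated measures ANOVA will be used if the data meet the sphericity assumption".
- **The non-normal method.** "a Friedman test will be used if the data do not meet the normal distribution". No rank-based method with a group or group-by-time term is named for this comparison.
- **The arms.** They are independent and parallel (Study design and setting): "Seventy GAD patients will be randomly allocated to either the combined abdominal massage and medication group or the medication-only group". Both take the same escitalopram regimen for eight weeks (Intervention).
- **Timing of HAMA.** Primary outcome says of its items: "which will be evaluated by professional psychiatrists before and after the treatment". The schedule figure is not available, so any further visits are unknown.
- **A separate rule.** For a plain comparison of measurement data between two groups, the same section says "a rank-sum test will be used for data that do not meet the normal distribution".

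**The concern.** The comparison is between arms, but the test named for non-normal data is a one-sample procedure for related measurements. Its null hypothesis is that the distribution does not shift across time points within patients. Whether patients are pooled or each arm is tested alone, a small p-value shows that scores changed, not that they changed more with massage.

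This matters because both arms receive an active drug. Improvement over eight weeks is the likely course in each, so a significant result is close to assured. If that p-value were reported as the comparison of the two groups, it would look like evidence of efficacy without being any.

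**Working it through.** **1. Inputs.** From Sample Size: SD 3.17, expected difference 2.76 HAMA points, two-sided α 0.05, power 90%, 29 evaluable and 35 randomised per arm. Assumed, because the article does not give them: within-patient correlation ρ = 0.5, a common fall of 2 to 5 points in both arms, and normal data with equal SD at each visit.

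**2. The plan's own figure.** Normal approximation: n = 2(1.960 + 1.282)² × 3.17² / 2.76² = 27.7, so 28 per arm. The independent two-sample t-test needs 28.7, so 29, with power 90.3%. The stated 29 per arm is reproduced. The trial is therefore sized for a comparison between independent arms.

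**3. The Friedman statistic.** For m patients and k occasions, with R_j the sum over patients of the within-patient ranks at occasion j:

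Q = 12 / [m k (k + 1)] × Σ R_j² − 3m(k + 1)

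Arm appears nowhere in it. Numerical check on 58 simulated patients with three occasions: Q = 2.172, p = 0.337. Subtracting 2.76 from every value in one arm left Q and p unchanged, as did reordering patients across arms.

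**4. Two occasions, exact calculation.** With k = 2 the statistic reduces to Q = (2x − m)² / m, where x is the number of patients whose score fell. This is a sign test of before against after. For m = 70, Q exceeds 3.841 when x ≥ 44 or x ≤ 26.

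- SD of change = 3.17 × √[2(1 − 0.5)] = 3.17.
- Common fall of 2: P(score falls) = Φ(2/3.17) = 0.736, and P(reject) = 0.983.
- Common fall of 5: P(score falls) = Φ(5/3.17) = 0.943, and P(reject) > 0.999.
- No change over time: P(reject) = 0.041.
- Sensitivity to ρ at a fall of 2: 0.930 for ρ = 0.3 and above 0.999 for ρ = 0.7. At a fall of 5 it exceeds 0.999 for both.

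**5. Simulation, 35 per arm, 4000 trials per row, ρ = 0.5.** With three visits the fall is linear over time.

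| Visits | Common fall | Arm difference | Friedman, pooled | Rank-sum on change |
|---|---|---|---|---|
| 2 | 0 | 0 | 4.2% | 5.0% |
| 2 | 2 | 0 | 98.2% | 5.1% |
| 2 | 5 | 0 | 100% | 5.0% |
| 2 | 5 | 2.76 | 100% | 93.6% |
| 3 | 0 | 0 | 5.2% | 4.9% |
| 3 | 2 | 0 | 98.2% | 4.7% |
| 3 | 5 | 0 | 100% | 4.7% |
| 3 | 5 | 2.76 | 100% | 94.4% |

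With a common fall of 5, Friedman rejects equally often with and without an arm difference. The rank-sum test on change holds its level and detects the difference. Running Friedman within each arm does not help: with 29 per arm and an assumed common fall of 6, it rejected in 100% of runs in both arms, with or without an added arm difference.

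**The case against.** The strongest reply is that the section already contains a valid non-parametric between-arm test. Non-normal HAMA scores at week 8 can be compared with the rank-sum test given for two-group data. Harm then requires three things together: non-normal data, the Friedman result read as an arm comparison, and that result preferred to the rank-sum result. This stands. The rejection rates above show what Friedman responds to; they are not the trial's false-positive risk. But the article does not say which of the two procedures decides efficacy, and the rank-sum sentence does not change what the longitudinal clause prescribes.

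Three stronger readings are tempting, and the document does not support them.

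- **A sphericity gap for HAMA.** The ANOVA branch depends on sphericity and the other on non-normality, so a reader might infer that normal but non-spherical data have no method. With the two HAMA occasions described, sphericity holds automatically and the gap cannot arise. For outcomes with more visits, corrections are detail that an analysis plan may hold.
- **A conflict with intention-to-treat.** A reader might infer that repeated measures ANOVA drops patients with missing visits and so contradicts "This study will conduct statistical analysis based on the principle of intention-to-treat (ITT"). That assumes no imputation. Handling of missing data may be set out in a plan that is not shown.
- **An invalid ANOVA branch.** With two occasions, its group-by-time test is equivalent to an independent t-test on change, which is a valid between-arm test. Nothing here requires replacing it.

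**Conclusion.** Wrong as written, but confined to one clause. For non-normal data, the test named for the over-time comparison of the arms cannot detect a treatment effect. That Friedman ignores arm is algebra and needs no assumption. The size, about 98% to 100% rejection with no arm difference, depends on the assumed common fall of 2 to 5 points and correlation of 0.5; at a correlation of 0.3 the lower end is 93%. It does not depend on whether there are two or three visits.

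A reader might infer that the trial is headed for a false claim of efficacy. The document does not support that much: such a claim would arise only if the Friedman p-value were taken as the arm comparison. The sample size is unaffected.

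**What to change.** - Delete the Friedman test for between-arm questions. In its place name a rank-based between-arm test, for example a rank-sum test on change from baseline, or a rank-based ANCOVA of the week-8 score adjusted for baseline.
- State that the treatment result is the arm contrast. In the ANOVA branch this is the group-by-time term, not the time effect.
- Keep Friedman, or a paired test, only for describing change within an arm.
- A mixed model with arm, visit and arm-by-visit would be an acceptable alternative but is not required.

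The cost is a change of analysis wording, best made before the data are analysed. It needs no new data and no more patients.

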## Abstract

Introduction and aim: Generalized anxiety disorder (GAD) is a prevalent mental health condition characterized by excessive, often uncontrollable anxiety, frequently accompanied by autonomic dysfunction symptoms. The gut-microbiota-brain axis is implicated in its pathogenesis. Traditional Chinese medicine therapies, including abdominal massage, are increasingly being considered for GAD treatment. This study is designed to evaluate the therapeutic potential of abdominal massage for GAD and its influence on patients' gut microbiota.

Materials and methods: A prospective, assessor-blinded, single-center randomized controlled trial involving 70 GAD patients, randomly allocated to either a combined abdominal massage and medication group or a medication-only group will be conducted. An additional 35 healthy individuals will serve as normal controls.

Results: The primary outcome measure will be the Hamilton Anxiety Rating Scale (HAMA) score pre- and post-treatment. Participants will undergo electroencephalogram (EEG) assessments and provide stool samples for gut microbiota evaluation. Differences between GAD patients and healthy controls will be compared, and changes in the two GAD groups pre- and post-treatment will be monitored. Subsequently, the correlation between EEG findings, gut microbiota, and clinical efficacy in GAD patients will be analyzed.

Conclusion: This study seeks to confirm the therapeutic benefits of abdominal massage for GAD and offer preliminary insights into its underlying mechanisms. Changes in these indicators before and after treatment in both the treatment and control groups will be examined to clarify the potential mechanisms by which abdominal massage may benefit GAD patients. Abdominal massage is hypothesized to alleviate clinical symptoms in GAD patients by modulating the gut-brain axis. If our hypothesis is validated, abdominal massage could emerge as a new alternative treatment for GAD and offer fresh insights into the mechanisms underlying massage therapy. The study's findings will be disseminated through peer-reviewed publications.

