Leveraging fecal 16S rDNA gene sequencing technology, this study will probe into the diversity, richness, and community structure of gut microbiota in GAD patients at a micro level. The regulatory effects of abdominal massage on gut microbiota will also be examined. This will further illuminate the gut-brain interaction mechanisms under the microbiota-gut-brain axis (MGBA) theory, demonstrating how abdominal massage contributes to the improvement of GAD.

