Based on prior research, the Hamilton Anxiety Rating Scale (HAMA) score for the medication group was 18.61±3.17 [14]. The HAMA score for the treatment group is anticipated to decrease by 2.76 points. With a two-sided significance level (α) of 0.05 and a power of 90%, the required sample size was calculated using PASS 2021 software. This resulted in a needed sample size of N1=29 for the treatment group and N2=29 for the control group. Taking into account a potential dropout rate of 20%, a minimum of 35 subjects per group is needed, amounting to a total of at least 70 subjects. In addition, 35 healthy participants will be included in the study.

Intervention

Treatment Group GAD Patients

The medication regimen for this study will consist of oral escitalopram (Bailex) (Sichuan Kelun Pharmaceutical Co., Ltd., China; approval no.: National Drug Standard H20080788; specification: 10 mg × 10 tablets) [15]. Each participant will take 10 mg once daily at 09:00 AM for a duration of eight weeks.

In addition to the medication, participants in the treatment group will receive abdominal massages. The massage procedure will follow guidelines from the "Tui Na" textbook [16] edited by Fang Min and Wang Jingui (5th edition, "14th Five-Year Plan" for higher education in TCM). Participants will lie in a supine position while the practitioner performs rhythmic circular motions on the abdomen with the palm, 5 minutes clockwise and 5 minutes counterclockwise, at a frequency of 120 times/min. This is followed by finger massage on Zhongwan, Tianshu, Qihai, and Guanyuan points for 5 minutes at a frequency of 160 times/min. The total treatment time is approximately 15 minutes, conducted once daily, five days a week, for eight weeks.

To ensure the quality of the abdominal massage and the precise location of the acupoints, several measures will be implemented. Prior to the trial, [name] massage techniques, including force and frequency, will be calibrated using the YF-3 Hand Technique Measurement Instrument to create a standardized model. During the trial, experienced physicians with over 10 years of clinical practice will carry out the procedures. Additionally, all operators will receive training to ensure their techniques align with the model established by the YF-3 instrument.

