This study aims to design a high-quality randomized controlled trial to observe changes in brain electrical activity and clinical efficacy indicators before and after the combined treatment of abdominal massage and escitalopram in GAD patients. EEG recordings will be used to analyze the spontaneous and rhythmic electrical activity of brain cell groups, focusing on brain discharge indices and changes in alpha rhythms. Additionally, fecal 16S rDNA gene sequencing technology will be employed to examine the diversity, richness, and community structure of gut microbiota in GAD patients, as well as the regulatory effects of abdominal massage on these microbiota. This will help further elucidate the brain-gut interaction mechanism through which abdominal massage improves GAD based on the gut-brain axis theory.

However, this study has certain limitations in its design. Firstly, due to the nature of the intervention, it is impossible to blind the patients and the massage therapists. To minimize performance and detection biases, allocation concealment will be implemented, and outcome measurements will be conducted by assessors who are unaware of group assignments and interventions. Secondly, a fixed massage treatment protocol will be used for all participants in the trial without differentiation, which may not fully demonstrate the efficacy of the massage. Additionally, the sample size is relatively small. These potential limitations might affect the results and necessitate future studies.

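### The single 0.05 level for all tests also covers the gut-microbiota comparisons and the EEG–microbiota–efficacy correlations, leaving error uncontrolled in a family meant to inform the mechanism

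*Protocol article*

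**What the plan says.** The Statistical analysis section lists t-tests, rank-sum tests, one-way and repeated measures ANOVA, the Friedman test and χ² tests for generic measurement, count and rank data. It then closes with "The significance level for all tests will be α=0.05". No outcome is exempted, and no adjustment for multiple tests is mentioned.

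Gut microbiota appears in the Results section under other outcome measures, apart from the primary outcomes. The Discussion sets out its content: "fecal 16S rDNA gene sequencing technology will be employed to examine the diversity, richness, and community structure of gut microbiota in GAD patients". The Abstract adds that "the correlation between EEG findings, gut microbiota, and clinical efficacy in GAD patients will be analyzed".

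On the use of these results, the end of the Objectives in the Introduction speaks of "demonstrating how abdominal massage contributes to the improvement of GAD". The Conclusions say that changes in these indicators will be studied to elucidate potential mechanisms of massage. The Abstract is more cautious and promises only preliminary insights into mechanism.

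**The concern.** A protocol that says nothing on multiplicity leaves the matter to the analysis plan. This one states a level for every test, and the plain reading is that each microbiota comparison and each correlation is judged on its own at 0.05. The family has at least three domains, several contrasts and a set of correlations, so the chance that something crosses 0.05 by luck exceeds 5%, and it grows with the number of features examined.

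The mechanistic reading is at stake. A taxon or a taxon–EEG correlation that crosses 0.05 by chance could be presented as part of how massage works. The Objectives wording invites that, and nothing in the stated rule guards against it. The HAMA comparison does not depend on this family.

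**Working it through.** **1. The plan's own figure.** The only derived figure that uses the 0.05 level is the sample size. Its inputs, from the Sample Size section, are "With a two-sided significance level (α) of 0.05 and a power of 90" (per cent), a HAMA "score for the medication group was 18.61±3.17", and "The HAMA score for the treatment group is anticipated to decrease by 2.76 points". The normal approximation is n = 2(z₀.₉₇₅ + z₀.₉₀)² (SD/δ)² = 2(1.960 + 1.282)² (3.17/2.76)² = 27.7, so 28 per group. With the noncentral t distribution, power is 0.892 at 28 and 0.903 at 29. This reproduces the "needed sample size of N1=29 for the treatment group and N2=29 for the control group". The level of 0.05 is therefore calibrated to one HAMA comparison. The calculation does not address the microbiota family.

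**2. Inputs for the multiplicity check.** The level per test is 0.05 (Statistical analysis), taken as two-sided as in the Sample Size section. The named domains are diversity, richness and community structure, so m = 3. Three contrasts bear on the randomized patients: between arms, and before versus after in each arm. That gives 3 × 3 = 9. The numbers of taxa, diversity indices and correlation pairs are not given, so m = 20 to 200 is an assumed range.

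**3. Formulas, with no true effect anywhere.**
- Expected false positives: 0.05 × m, whatever the correlation.
- Chance of at least one, independent tests: 1 − 0.95^m. For m = 3, 1 − 0.8574 = 0.143. For m = 9, 1 − 0.6302 = 0.370. For m = 100, 1 − 0.0059 = 0.994.
- Chance of at least one, test statistics equally correlated at ρ: 1 − ∫ [Φ((z − √ρ·g)/√(1−ρ)) − Φ((−z − √ρ·g)/√(1−ρ))]^m φ(g) dg, with z = 1.96, evaluated numerically. Simulation gives the same values to within about one percentage point.

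| Tests m | Expected false positives | ρ = 0 | ρ = 0.5 | ρ = 0.8 |
|---|---|---|---|---|
| 3 (one per domain) | 0.15 | 14% | 13% | 10% |
| 9 (3 domains × 3 contrasts) | 0.45 | 37% | 27% | 17% |
| 20 (assumed) | 1.0 | 64% | 42% | 22% |
| 50 (assumed) | 2.5 | 92% | 62% | 30% |
| 100 (assumed) | 5.0 | 99.4% | 78% | 36% |
| 200 (assumed) | 10.0 | over 99.9% | 90% | 42% |

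Reaching 90%, 95% and 99% takes 45, 59 and 90 independent tests.

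**4. Which contrast speaks to massage.** Healthy participants give samples only at enrollment (Intervention, Healthy Participants), so the patient–healthy contrast cannot show a response to massage. Both arms take escitalopram for eight weeks, so a before–after change within an arm need not be null even if massage has no effect on the microbiota. The massage question therefore rests on the between-arm difference in change. The nine-test row applies only if all nine hypotheses are null.

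**The case against.** The strongest reply is that the article is condensed. It describes no 16S method and no correlation method, and such detail, including adjustment at taxon level, commonly sits in the full protocol or analysis plan. A level of 0.05 can also be applied to adjusted p-values, since the sentence neither says unadjusted nor forbids adjustment. The microbiota is not a primary outcome, the Abstract calls the insights preliminary, the mechanisms are called potential, and the Discussion admits a small sample and the need for further studies.

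Much of this stands. The missing pipeline is not an error, and it would be wrong to say that the plan excludes false-discovery control or carries no hedge at all. A reader might also infer that the plan commits to testing taxon by taxon, or to a large grid of correlations. The text does not say so. Nor does it give a rule by which any single significant feature would confirm the gut–brain hypothesis.

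The stated sentence remains. It sets one level for all tests, names no exception and mentions no adjustment, so an analyst who follows it literally would apply 0.05 to each test. The cautious words in the Abstract change no decision rule, and they sit uneasily with the stronger claim in the Objectives.

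**Conclusion.** The point holds as a defect in a stated rule for a secondary family. Even with one test for each of the three named domains, the chance of a false positive is 10% to 14%, or two to three times 0.05. For nine tests it is 17% to 37%. Larger figures depend on an assumed number of tests: at 100, from 36% (ρ = 0.8) to over 99% (independent), with five false positives expected throughout.

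A reader might go further and infer that spurious massage-responsive features are near certain. The documents do not support that. It would take roughly 60 to 100 or more largely independent tests, a number stated nowhere, and strong correlation between features lowers the risk considerably. The healthy-control contrast cannot add to that particular error either.

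The figures rest on a global null, a two-sided 0.05 level per test and, where correlated, equal correlation between tests. The change is worth making before analysis. It does not touch the HAMA comparison, and whether HAMA and EEG together need an adjustment is a separate matter.

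**What to change.** Keep the 0.05 sentence in Statistical analysis for the other outcomes, so that EEG, HAMD and SCL-90 are not left without a level, and add wording such as:

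*Gut-microbiota feature-level tests and the correlations among EEG, microbiota and clinical efficacy are exploratory. They are reported with Benjamini–Hochberg adjusted p-values (false discovery rate 5%) within each contrast. The between-arm difference in change is the main contrast for any effect of massage.*

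One global test of community structure could be added. A distance-based permutation test is one option among several, and it is not essential. If no feature truly differs, the false discovery rate equals the chance of any false declaration, so this adjustment brings that chance back to 5% for independent tests within each contrast.

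In the Objectives, replace *demonstrating how* with *exploring whether*, in line with the Abstract's description of the insights as preliminary.

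No new patients, samples or visits are needed. The costs are a few lines of text and code, possibly software beyond base SPSS, fewer features declared significant, and a mechanistic message that is openly hypothesis-generating.
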